## Abstract

**Background:**

Self-management plays a vital role in noncommunicable disease prevention and control. However, it has been challenging for patients and their caregivers to identify how much their lifestyle affects their health and what level of effort they should make to reduce cardiovascular disease (CVD) risks in everyday life. Therefore, knowing their own CVD risk and daily health-related situations will provide relevant information for self-management by those at risk. The need to help individuals understand their relevant information creates an opportunity to investigate whether and how to implement a combined digital and nurse-led self-management intervention in a real-world community setting.

**Objective:**

This study aims to evaluate the effectiveness of a combined approach combining digital device support, including a smartwatch, a mobile app, and a salt meter, with nurse-led case management, on self-management behaviors and clinical outcomes.

**Methods:**

This study uses a combination of a nurse-led self-management with a digital and mobile health innovative approach, including tailored small group face-to-face education sessions, a smartwatch, a smartphone health app, and a salt meter, to increase the self-management behaviors to reduce vascular risk through designing and testing an integrated community-based strategy targeted at adults and older adults at risk of CVD in Thailand. The study uses a single-arm pretest-posttest design to assess the intervention’s effects. The intervention will consist of the following components: (1) an interactive face-to-face education session; (2) a real-time knowing your numbers strategy using a smartwatch, a smartphone health app, and a salt meter; (3) a mindfulness-based stress management strategy using Somporn Kantaradusdi-Triamchaisri technique meditation healing exercise; and (4) a self-management diary. Quantitative data will be collected using a smartwatch, a salt meter, a food diary, and questionnaires at baseline and at the end of week 6. Clinical outcomes will be assessed at baseline, primary end point (wk 12), and secondary end point (wk 24).

**Results:**

This study, funded in January 2025, will involve 45 patients. We received ethical approval on May 31, 2024, and began recruitment for participation in May 2025. Researchers will collect, analyze, and synthesize to evaluate the study procedure. We expect to complete data collection by December 2025, with the first results submitted for publication in March 2026.

**Conclusions:**

The implementation of a combined digital device and nurse-led case management may identify the use of digital health to support self-management and improve vascular health. The findings of this study will provide insights for a large-scale randomized controlled trial and for ongoing improvements in the noncommunicable disease care system.

## Introduction

### Background

Cardiovascular diseases (CVDs) are a leading cause of noncommunicable diseases (NCDs) globally. CVDs consist of ischemic heart disease, rheumatic heart disease, hypertensive heart disease, stroke, and other cardiovascular conditions [1]. CVD caused 20.5 million deaths in 2021, as reported by the World Heart Federation. The death rates from CVDs remain steady in low- and middle-income countries, where over 80% of global CVD deaths occur [2,3]. In 2021, CVD was the leading cause of death and disability-adjusted life years (DALYs) globally, accounting for 26.8% of total deaths and 14.9% of total DALYs 2,3[4]. The American Heart Association reports a significant rise in CVDs worldwide, with heart attacks and strokes being 4 out of 5 causes of CVD deaths [5]. From 1990 to 2021, ischemic heart disease increased by 68%, stroke by 44%, hypertensive heart disease by 87%, and cardiomyopathy and myocarditis by 48% [5]. In Thailand, stroke has significantly increased every year, with an average of 8350 cases per year from 2563 to 2567 and increased to 21,012 cases or 15.28% from 2022 to 2023 and 20.77% death rate in 2024 [6]. Additionally, CVD prevalence in rheumatoid arthritis patients was higher in women with diabetes mellitus, hypertension, and dyslipidemia in Thailand [6].

The risk of CVD is associated with several common risk factors such as age, diabetes, high blood pressure, high cholesterol, a family history of vascular or heart disease, obesity, and smoking, such as an improper perception of health, a diminished sense of control, limited availability of health information, inadequate self-management skills, delayed and inefficient communication between health care providers and patients, and insufficient instrumental support [5,7,8]. Managing these risk factors through self-management intervention can help prevent or minimize the onset of vascular complications [6,9]. Therefore, encouraging self-management is crucial for preventing and controlling CVD. Self-care is a naturalistic decision-making process that addresses both the prevention and management of chronic illness, with core elements including self-care maintenance, self-care monitoring, and self-care management [10]. Self-management refers to a patient’s ability to cope with all aspects of a chronic illness, including symptoms, treatment, physical and social consequences, and lifestyle changes [6]. Several literature reviews have found that self-management strategies incorporating lifestyle modifications and behavioral interventions have been shown to improve vascular health [10-13].

Successful management of CVD risk involves interactive group education on the disease and its management, combined with regular monitoring and provision of feedback [9,10]. It also includes providing equipment and lifestyle advice supported by dietary and physical activity guidance, weight reduction, stress management, and medication adherence [11,14]. In NCD self-management, nurses play a crucial role in supporting patients with uncontrolled chronic conditions by providing health education, counseling, coaching, and support [13]. However, it has been challenging for patients and their caregivers to identify how much their lifestyle affects their health and what level of effort and intensity they should make to lower CVD risks in everyday life. Therefore, knowing their own CVD risks and daily health-related situations will provide relevant information and motivation for self-management among those at risk. Digital health interventions (DHIs) have become recognized as an effective complementary strategy [7,9,15-17] to enhance self-management support, as they overcome barriers and time constraints that traditional self-management approaches often encounter.

Interest in using smartwatches and digital technologies to develop DHIs that improve health and well-being has risen in recent years. Several reviews have reported that the effects of DHIs, including telemedicine, mobile health, and decision support tools, have enabled virtual access to clinical care, fostered positive health behaviors, and shown improvements in health outcomes and health care delivery for CVD, thereby improving CVD health [7,15,17-19].

Even though DHIs have proven to be effective in enhancing self-management behaviors and promoting clinical health outcomes, DHIs have been challenging in resource-limited settings [20]. The combination of DHIs and health care providers’ interventions can potentially help patients with NCD improve adherence to self-management when compared with stand-alone DHIs [7]. A systematic review found that smartwatch interventions in the everyday lives of patients aged ≥50 years help support lifestyle changes, improve treatment adherence, and improve clinical outcomes for CVD [19,21]. Recent smartwatch technology, which connects to a mobile app, has enabled lifestyle, goal tracking, and interactive communication interventions, thereby fostering virtual access to clinical care and promoting positive health behaviors that lead to achieving clinical outcomes [17,21,22]. The evaluation of the implementation strategy in smartwatch and digital health research studies, especially in Thailand, is limited [21]. This limitation presents an opportunity to investigate whether and how a combined DHI and nurse-led self-management intervention promotes vascular health in a real-world, resource-limited setting with diverse health determinants in Thailand.

Poor eating habits are a significant risk factor for NCD, especially CVDs. The Dietary Approaches to Stop Hypertension (DASH) diet emphasizes vegetables, whole grains, lean protein, and low-fat dairy, while limiting sodium, unhealthy fats, and sugary beverages. It is particularly beneficial for cardiovascular health, especially for those with hypertension [23]. Research shows it effectively lowers blood pressure, with reductions of −3.89 mm Hg systolic and −2.19 mmHg diastolic compared to control diets [24]. Additionally, the DASH diet has a positive impact on other cardiovascular risk factors, including blood pressure, triglycerides, cholesterol levels, body weight, and BMI [23,25,26]. The duration of DASH diet interventions varies. A study found that the DASH diet reduced 10-year atherosclerotic CVD risk scores by about 10% in just 8 weeks [27]. The DASH-sodium trial noted significant reductions in cardiac injury and inflammation markers over 12 weeks [28]. Additionally, a systematic and meta-analysis review suggested that a duration of 12 weeks or more is particularly effective for achieving reductions in body weight, BMI, total cholesterol, and low-density lipoprotein cholesterol [29].

Overall, these findings suggest that the DASH diet can offer significant cardiovascular benefits within 8 to 12 weeks, with longer adherence potentially enhancing these effects. However, this study uses a 12-week intervention to assess its outcomes. Participants in this study will use digital devices only for the first 6 weeks, then engage in self-management activities for another 6 weeks. These findings highlight the significant benefits of the DASH diet in enhancing cardiovascular health by addressing multiple risk factors and biomarkers associated with hypertension and CVD. Overall, the DASH diet stands as a well-supported dietary intervention for improving cardiovascular health in individuals with hypertension, with evidence indicating its broader applicability across various populations and health conditions.

Excessive salt intake is a significant risk factor for hypertension, a leading cause of NCDs in Thailand [30,31]. Studies suggest that each 1 g increase in sodium intake above the reference level would result in a 2.11 mmHg increment in systolic blood pressure (BP) and a 0.78 mm Hg increment in diastolic BP [31]. Salt meter, a device used to detect sodium content in daily food, is crucial in Thailand for testing and managing NCD, especially hypertension and CVD [31]. Since a salt meter can tell individuals about their sodium intake, it helps them manage their salt consumption habits. A randomized controlled study found that using a salt meter for self-monitoring of salt intake, in conjunction with dietary education, was superior to education alone in patients with hypertension, resulting in better BP control [31].

Excessive salt intake significantly increased the risk of hypertension, stroke, and total CVD [32], a leading cause of NCDs in Thailand [23,24]. A salt meter is crucial for testing and managing NCDs in Thailand, particularly hypertension and CVD [24].

As tailored self-management services and digital health devices are not equally accessible, we need to investigate if, when used with nurse-led self-management, a generic smartwatch and a salt meter can be used to supply individuals with mild to moderate CVD risk with the estimated reference information to guide daily self-management behaviors and whether the use of digital devices for a short duration can offer a carry-on estimation to guide self-management behaviors to lower CVD risk.

This study will address the gap between face-to-face and DHIs for improving self-management behaviors in urban and suburban settings in Thailand by empowering individuals with NCDs to take proactive steps to manage and engage in self-care in their daily lives. This study aims to evaluate the effectiveness of tailored, context-specific education and mobile health engagement, including the use of smartwatches, smartphones, and salt meters, in promoting self-management behaviors. Tailored, case-specific, and context-specific education, digital engagement, real-time information supply, and free primary care access are all critical for improving perceptions of risk, increasing literacy in, and motivating improvements in CVD-related health behaviors. General and reasonable smartwatches may help people get a snapshot of their daily health information, which they will use as a reference to adjust their diet, exercise, stress management, and sleep habits to meet their anticipated everyday milestones. The findings may offer practical guidance for nurses and health care professionals managing CVD in Thailand and contribute valuable insights for shaping future health care policies.

### Objectives

This study aims to investigate whether a combined approach involving digital device support, including a smartwatch, a mobile app, and a salt meter, coupled with nurse-led case management, can enhance self-management behaviors and improve clinical outcomes.

### Hypotheses

We have three primary hypotheses. First, we hypothesize that patients with chronic diseases who are at mild to moderate cardiovascular risk will report overall acceptable satisfaction with the mobile digital interventions. Second, we hypothesize that participants will use digital-based information as a reference to adjust their self-management behaviors in response to the nurse’s tailored interventions over 6 weeks. Third, we hypothesize that participants will exhibit improved self-management behaviors at weeks 6, 12, and 24, better clinical outcomes, and reduced CVD risks at both the end of week 12 (primary endpoint) and 3 months posttreatment (week 24; secondary end point).

## Methods

### Study Design

This study uses a single-arm pretest-posttest design to assess the effects of the intervention (Figure 1). The study was perofrmed per the SPIRIT checklist (Checklist 1)[33].

**Figure 1. F1:**
[figure not shown]
Study design flowchart. NCD: noncommunicable disease.

### Study Components

#### Overview

To increase self-management behaviors and reduce vascular risk among adults and older adults at risk of CVD, this study provides interactive group education on vascular health and its management, accompanied by condition monitoring and feedback (Figure 2).

The intervention will consist of the following components: (1) a nurse-led tailored self-management session with an interactive face-to-face education, (2) a real-time knowing your numbers strategy using a smartwatch, a smartphone health app, and a salt meter, (3) a mindfulness-based stress management strategy using the Somporn Kantaradusdi-Triamchaisri (SKT) meditation healing exercise, and (4) a self-management manual. We will ask all participants to engage in self-management behaviors for 6 weeks and to continue their self-management practice without digital devices for an additional 6 weeks.

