#### A Real-Time Knowing Your Numbers Strategy

This study component comprises the use of a smartwatch, a smartphone health app, and a salt meter. We will ask participants to use these digital devices for 6 weeks.

##### A Smartwatch: Huawei Watch Fit 3

This study will use the commercialized Huawei Watch Fit 3 and its associated HUAWEI Health app (Huawei Technologies Co, Ltd). Study participants will use this smartwatch and its smartphone app to collect daily reference data on physical activity, sleep quality, heart rate, and stress levels, which will guide their daily self-management efforts and actions in line with their target setting with the nurses. The device features a built-in interactive function that allows each participant to set goals for exercise, physical activity, and sleep. The health app helps participants track their progress and compare milestones on a weekly and monthly basis. For instance, if a participant misses a walking target, they can take additional steps in their daily routine. Participants can continue using the health app to track their physical activity after using this wearable device. Similarly, participants can use sleep information from a prior night to improve their sleep hygiene.

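### The protocol ends digital device support at week 6 but lets participants keep using the health app, so weeks 12 and 24 cannot be read cleanly as carry-over without devices

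*Protocol article*

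**What the plan says.** **The app belongs to the device support.** The Objectives describe "digital device support, including a smartwatch, a mobile app, and a salt meter". The section on the real-time knowing-your-numbers strategy opens with "This study component comprises the use of a smartwatch, a smartphone health app, and a salt meter" and continues "We will ask participants to use these digital devices for 6 weeks".

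**Device support ends at week 6.** The Background says "Participants in this study will use digital devices only for the first 6 weeks, then engage in self-management activities for another 6 weeks". The Overview of Study Components has participants "continue their self-management practice without digital devices for an additional 6 weeks". The section on the self-management manual also gives the digital components a length of six weeks. The Conclusions name the watch, the app and the salt meter together and assign all three to the first six weeks.

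**The app may continue.** The smartwatch subsection says "Participants can continue using the health app to track their physical activity after using this wearable device". It gives no end date, and nothing limits the permission to the first six weeks.

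**The question asked of the later period.** The Background wants to know "whether the use of digital devices for a short duration can offer a carry-on estimation to guide self-management behaviors to lower CVD risk".

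**The concern.** The protocol describes the exposure between week 6 and the later assessments in two incompatible ways. On one description, participants work from what they learned in the first six weeks. On the other, some of them still have a tracking tool that belongs to the intervention. According to the smartwatch subsection, the app lets users follow their progress and set one week's or month's milestones against another's, so continued use is continued exposure to an intervention component.

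The interpretation of the later assessments is at stake. If scores hold up at weeks 12 and 24, a report could present this as behaviour that lasts once devices are withdrawn. Under the permission, the same result could come from a mix of people with and without the app. The trial has one arm, so no comparison group can separate the two. The study is meant to inform a randomised trial, whose designers would want to know whether any sustained change occurred with or without the app.

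**Working it through.** No figure in the protocol tests this point, so the check compares the text and then bounds the consequence.

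**Step 1: is the app a digital device in the protocol's own terms?** Yes. The Objectives, the knowing-your-numbers section and the Conclusions all list it with the watch and salt meter. The Conclusions also place it in the first six weeks, which rules out a reading in which the devices are only the watch and salt meter.

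**Step 2: do the statements conflict?**

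| Place | Digital support after week 6 |
|---|---|
| Background | Devices only in the first 6 weeks |
| Overview of Study Components | None in the following 6 weeks |
| Vascular care self-management manual | Digital components last 6 weeks |
| Conclusions | Watch, app and salt meter in the first 6 weeks |
| Smartwatch subsection | App may continue for physical activity, no end date |

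All five are current text. The last cannot hold together with the other four as worded.

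**Step 3: how much time is affected?**
- Before the primary end point: 12 − 6 = 6 of 12 weeks.
- Before the secondary end point: 24 − 6 = 18 of 24 weeks.

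The Overview's device-free statement reaches only to week 12. For weeks 12 to 24 the conflict rests on the Background, the manual section and the Conclusions, which confine the digital components to the first six weeks.

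**Step 4: how much of the primary outcome is directly exposed?** The CVD Self-Management Behavior Questionnaire has 17 items scored 0 to 5: 4 on exercise, 6 on diet, 5 on treatment compliance and 2 on smoking.
- Share of items: 4/17 = 23.5%.
- Share of points, assuming items are summed: 4 × 5 = 20 of 17 × 5 = 85.
- Items on matters that the permission does not mention: 6 + 5 + 2 = 13 of 17.

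If a share *p* of participants keeps the app and their exercise items are *x* points higher because of it, the mean total score rises by *p* × *x*, with *x* at most 20. The protocol gives neither *p* nor *x*, so only this ceiling can be stated, and it is not an expected value. It covers the direct route only. Blood pressure, BMI, lipids, HbA1c and CVD risk could also move through activity.

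**Step 5: would the planned data show the mix?** Data Collection Procedures describe weekly monitoring for six weeks. The Conclusions place digital engagement at the end of week 6. No stated measure covers app use afterwards. The cloud data listed are physical activity, sleep, heart rate and stress, collected with the watch. Whether app-only data reach the cloud once the watch period ends is not said.

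**The case against.** The strongest reply is that the objective and the primary outcome concern the combined programme, not the withdrawal of devices. Carry-over appears only in the Background, and the sentence that raises it names the smartwatch and salt meter rather than the app. This largely stands. A reader might infer that the week-12 and week-24 end points fail to measure what the trial set out to measure. The documents do not support that, because both remain valid readings of the programme as delivered.

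Second, the permission is optional and confined to physical activity. The smartwatch subsection gives goal-setting to the device and credits the app with tracking and comparison. This also stands, and it limits the direct effect as shown above.

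Third, the Discussion already says that a single-arm design cannot establish causality and names secular trends, regression toward the mean and behavioural reactivity to monitoring. That covers causal claims in general. It does not cover describing a period as device-free when the protocol allows a device component in it.

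Fourth, an article leaves detail to the full protocol. That would excuse a missing app-use variable alone. It does not excuse two conflicting statements of the exposure period in the article itself.

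**Conclusion.** The contradiction is certain and rests on the protocol's own definitions. Its consequence is moderate. If the smartwatch subsection governs, the results at weeks 12 and 24 combine carry-over with continued app support in unknown proportion, mainly for the exercise items (4 of 17) and for clinical outcomes that activity may affect. If the Overview governs, the period is device-free and only the wording needs repair.

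Two further inferences are tempting but unsupported. One is that the carry-over effect would be overstated by some particular factor. The documents give no share of continuing users and no effect of continued use, so no such factor can be calculated. The other is that participants who drop the app show the true device-free effect. They choose to stop after baseline, and if those who continue are the more motivated (an assumption), the non-users would probably understate carry-over in the whole group.

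This is a cheap improvement to wording and data collection. It is not a flaw that invalidates an end point. The share-of-points figure assumes that questionnaire items are summed.

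**What to change.** 1. Reconcile the Background, the Overview of Study Components, the smartwatch subsection, the manual section and the Conclusions by stating which digital components end at week 6. Which rule applies is for the investigators to decide.
2. If app use may continue, ask each participant one question about it at the week-12 and week-24 visits. Add cloud activity data if app-only data turn out to be available there.
3. Report the proportion of continuing users, and the week-12 and week-24 changes overall and by later app use. Label the split descriptive and self-selected, and do not present the non-user group as an unbiased estimate of carry-over.
4. In that case, describe the overall result as the change after the watch and salt meter period with optional app use, not as device-free.

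The cost is a few sentences and one extra question at visits already planned. The limitation is that the subgroups will be small and not randomised: 45 participants are planned in all, with 30% attrition allowed for.
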